**10.10.3.2. Anti-HBs antibodies**

The seroprotective level for anti-HBs is  $\geq 10$  mIU/mL. The percentage of subjects with protective levels of anti-HBs ( $\geq 10$  mIU/mL) with 95% confidence interval (95% CI) will be determined at each blood sampling time point. Antibody titers will be summarized by GMT with 95% CI. Tables will be generated by vaccine group and by protection status (protected subjects are those recipients of RTS,S/AS01E who are not diagnosed with malaria meeting the primary case definition within the 4½ month ACD period). Antibody titers after the third dose will also be investigated using reverse cumulative curves. Comparisons between protected and non-protected may be performed using Wilcoxon Rank Sum tests.

**10.10.3.3. Frequency of T-cells specific to CS**

The frequency of T-cells specific to CS will be identified as CD4/CD8 + T-cells expressing at least two cytokines amongst CD40L, IL-2, TNF- $\alpha$  and IFN- $\gamma$  upon a short term in vitro stimulation with a pool of peptides covering the vaccine CS portion. Results will be expressed as CS-specific CD4/CD8 T-cells per million respectively of CD4 or CD8+ T-cells. Descriptive statistics (N, minimum, Q1, median, Q3, maximum, mean, standard deviation) will be tabulated by group and protection status, for pre and post vaccination timepoints (pre and 1 month post Dose 3) (protected subjects are those recipients of RTS,S/AS01E who are not diagnosed with malaria meeting the primary case definition within the 4½ month ACD period). Analysis by protection status will be limited to recipients of RTS,S/AS01E. Results will also be presented graphically by box plots. Between group comparisons and between protection status comparisons will be performed by non-parametric Wilcoxon Rank Sum tests. Within group comparisons (i.e. comparing post versus pre timepoint within the RTS,S group) will be performed by Wilcoxon Signed Rank test for paired samples.

**10.10.3.4. Exploratory immunogenicity endpoints**

The frequency of T-cells specific to CS will be identified as cytokine secreting/expressing cells using cytokine ELISPOT assay or intracellular cytokine assays. Descriptive statistics (N, minimum, Q1, median, Q3, maximum, mean, standard deviation) will be tabulated by group and protection status, for pre and post vaccination timepoints (pre and 1 month post Dose 3), when available (protected subjects are those

recipients of RTS,S/AS01E who are not diagnosed with malaria meeting the primary case definition within the 4½ month ACD period). Results will also be presented graphically by box plots. Between group comparisons and between protection status comparisons will be performed by non-parametric Wilcoxon Rank Sum tests. Within group comparisons (i.e. comparing post versus pre timepoint within the RTS,S group) will be performed by Wilcoxon Signed Rank test for paired samples.

#### **10.10.4. Analysis of safety**

##### **10.10.4.1. Secondary safety endpoints**

Safety will be analyzed on the Total Vaccinated Cohort. If the percent of enrolled subjects excluded from the ATP cohort for analysis of safety is more than 5%, a second analysis based on this ATP cohort will be performed to complement the Total Vaccinated Cohort analysis.

Analysis of the occurrence of SAEs will be performed on the Total Vaccinated Cohort. The proportion of subjects with an SAE, classified by the MedDRA preferred term level, reported from study start until Clinic Visit 6 (end of the double-blind phase) will be tabulated with exact 95% CI.

The proportion of subjects reporting an AE (unsolicited) 30 days post each vaccination, classified by the MedDRA preferred term level, reported from study start until the end of the double-blind phase will be tabulated with exact 95% CI.

The percentage of subjects with at least one local adverse event (solicited and unsolicited), with at least one general adverse event (solicited and unsolicited) and with any adverse event during the solicited follow-up period will be tabulated with exact 95% CI after each vaccine dose and overall. The percentage of doses followed by at least one local adverse event (solicited and unsolicited), by at least one general adverse event (solicited and unsolicited) and by any adverse event will be tabulated, overall vaccination course, with exact 95% CI. Similar tables will be generated for Grade 3 events, the relationship of the event to vaccination.

The percentage of subjects reporting each individual solicited local and general adverse event during the solicited follow-up period will be tabulated with exact 95% CI. The percentage of doses followed by each individual solicited local and general adverse event will be tabulated, overall vaccination course, with exact 95% CI. Similar tables will be generated for Grade 3 events, the relationship of the event to vaccination and for fever and temperature in 0.5°C increments.

Biochemistry (ALT and creatinine) and hematology (hemoglobin, WBC, platelets) values that are outside of the reference ranges will be described for Clinic Visit 6 (end of double-blind phase). Frequency distribution of results by toxicity grades will be tabulated by group.

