Subsequently, a large safety, immunogenicity and efficacy trial in children aged 1 to 4 years from an area of high transmission was conducted in Mozambique, enrolling a total of 2022 subjects (Malaria-026 [Report, GSK data on file]; [Alonso 2004]; [Alonso 2005]). In this study, 3 doses of RTS,S/AS02A (0.25 mL dose) were administered according to a 0, 1, 2-month schedule to approximately 1000 children. The primary endpoint of this trial investigated vaccine efficacy against the onset of clinical malaria disease. Up to six months post Dose 3, the VE determined as the time to the first clinical episode (after adjustment for covariates) was 29.9% (95% CI: 11.0 to 44.8;  $p = 0.004$ ). For the entire study period, up to 18 months post Dose 3, VE for the same endpoint was 32.8% (95% CI: 20.1 to 43.4;  $p = 0.0001$ ).

The trial also offered the opportunity to investigate VE against multiple attacks of malaria and severe malaria. Against multiple attacks, VE was 27.4% (95% CI: 6.2 to 43.8;  $p = 0.014$ ) up to six months post Dose 3. For the entire study period, VE was 32.4% (95% CI: 17.6 to 44.5;  $p = 0.0001$ ). Against severe malaria, VE was 57.7% (95% CI: 16.2 to 80.6;  $p = 0.019$ ) over six months post Dose 3: for the entire study period VE was 48.6% (95% CI 12.3 to 71.0;  $p = 0.02$ ).

During the single-blind phase (Months 8½ to 21) in both Cohort 1 and 2, the proportion of children experiencing a SAE was similar in the RTS,S/AS02A and control groups

(5.1% vs. 6.8%, respectively). However, in the overall surveillance period (Months 0 to 21), there was a tendency for the proportion of children experiencing a SAE to be lower in the RTS,S/AS02A group compared to the control groups in both Cohorts 1 and 2 (20.9% vs. 28.6%, respectively). The pattern of morbidity was similar to that previously observed at the study site and described in the region. At least 97% of recipients of RTS,S/AS02A were seropositive for anti-CS antibodies and at least 97% of recipients of RTS,S/AS02A were seroprotected for anti-HBs antibodies 18 months post Dose 3 [Alonso, 2005].

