### 4.2.2. KEMRI: Malaria Epidemiology

The primary vector of malaria is *An. gambiae*; *An. funestus* also occurs in large numbers in the south of the district. The EIR is estimated to be up to 100 infective bites per person per year [Mbogo 2003]. Transmission of malaria tends to be highest between April and August.

Historically the use of bed nets has been low (<5%). In the last few years however partnerships between various NGOs and the Ministry of Health have enabled the distribution of large numbers of bed nets in the Kilifi District. Recent surveying has shown that among 1 to 5 year old children, bednet use has increased from 35% at the start of 2005 to 70% at the end of 2005.

Malaria is the commonest cause for children under the age of 18 months to be admitted to hospital.

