## **5.8. Management and treatment of malaria in all subjects**

Children with malaria that can be treated with oral medication will receive a 6-dose regimen of Coartem® (artemether/lumefantrine, Novartis AG, Zurich, Switzerland), as advocated by WHO [World Health Organization 2005] and the governments of Kenya and Tanzania.

Children who require parenteral treatment will be admitted and receive treatment with quinine, which is standard practice and effective therapy in both Kenya and Tanzania.

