## 8.2. Definition of a serious adverse event

A serious adverse event (SAE) is any untoward medical occurrence that:

- a. results in death;
- b. is life-threatening;

*NOTE: The term 'life-threatening' in the definition of 'serious' refers to an event in which the subject was at risk of death at the time of the event. It does not refer to an event, which hypothetically might have caused death, if it were more severe.*

- c. requires hospitalization or prolongation of existing hospitalization;

*NOTE: In general, hospitalization signifies that the subject has been detained (usually involving at least an overnight stay) at the hospital or emergency ward for observation and/or treatment that would not have been appropriate in the physician's office or out-patient setting. Complications that occur during hospitalization are AEs. If a complication prolongs hospitalization or fulfills any other serious criteria, the event is serious. When in doubt as to whether 'hospitalization' occurred or was necessary, the AE should be considered serious.*

*Hospitalization for elective treatment of a pre-existing condition that did not worsen from baseline is not considered an AE.*

- d. results in disability/incapacity;

*NOTE: The term disability means a substantial disruption of a person's ability to conduct normal life functions. This definition is not intended to include experiences of relatively minor medical significance such as uncomplicated headache, nausea, vomiting, diarrhea, influenza, and accidental trauma (e.g. sprained ankle) which may interfere or prevent everyday life functions but do not constitute a substantial disruption.*

- e. medical or scientific judgment should be exercised in deciding whether reporting is appropriate in other situations, such as important medical events that may not be immediately life-threatening or result in death or hospitalization but may jeopardize the subject or may require medical or surgical intervention to prevent one of the other outcomes listed in the above definition. These should also be considered serious. Examples of such events are invasive or malignant cancers, intensive treatment in an emergency room or at home for allergic bronchospasm, blood dyscrasias or convulsions that do not result in hospitalization;

In this study all seizures occurring within a 30-day period of vaccination will be notified as SAEs [refer to Bonhoeffer, 2004]. Key information pertaining to seizures will be documented in the CRF.

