#### **Safety**

- Occurrence of SAEs throughout the entire study period.

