### **10.11.2. Analysis of safety**

Analysis of the occurrence of SAEs will be performed on the Total Vaccinated Cohort. The proportion of subjects with an SAE, classified by the MedDRA preferred term level, reported from study start until Clinic Visit 7 *and from study start until Clinic Visit 9* will be tabulated with exact 95% CI.

*Amended 17 April 2008*

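### SAEs are tabulated by preferred term with no summary of non-malaria SAEs, so a balanced or favourable SAE total cannot exclude an excess spread over several other terms

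*Protocol*

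**What the plan says.** For the double-blind phase, Section 10.10.4.1 specifies "The proportion of subjects with an SAE, classified by the MedDRA preferred term level, reported from study start until Clinic Visit 6", with exact 95% CI, on the Total Vaccinated Cohort. For the annex, Section 10.11.2 specifies "The proportion of subjects with an SAE, classified by the MedDRA preferred term level, reported from study start until Clinic Visit 7", and likewise to Clinic Visit 9. The tertiary safety endpoint in Section 10.3 covers any cause: "Occurrence of SAEs throughout the entire study period". The protocol defines no SAE summary that leaves malaria out and no grouping above preferred term. It does not exempt malaria from SAE reporting.

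Three other places make malaria part of the SAE count:

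- Section 8.2 makes serious any event that "requires hospitalization or prolongation of existing hospitalization".
- Section 5.8 says "Children who require parenteral treatment will be admitted and receive treatment with quinine".
- Section 4.2.2, on the Kilifi site, says "Malaria is the commonest cause for children under the age of 18 months to be admitted to hospital". Section 4.1 has no matching statement for Korogwe.

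Malaria is also the primary efficacy endpoint (Section 10.1).

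**The concern.** In most vaccine trials the overall SAE proportion is a fair first look at harm. Here it mixes harm with benefit. If the vaccine works, malaria admissions fall and take the SAE total down with them. A total that is equal between groups, or lower with vaccine, is then what one expects from efficacy and is weak evidence that other serious events are not increased. Section 1.4 shows the pattern for the related RTS,S/AS02A vaccine: SAEs in 20.9% of vaccinees against 28.6% of controls over Months 0 to 21, in a trial that also reported efficacy against severe malaria.

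The preferred-term rows help only in part. Malaria appears on its own line, and an excess concentrated in one other term would show. An excess spread thinly over several terms would be split into sparse rows. The proportion of children with at least one non-malaria SAE cannot be rebuilt exactly from those rows, because one child may contribute several terms.

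**Working it through.** **The plan's own figures.** The protocol gives no calculation for SAEs. Its efficacy design reproduces: 400 × 0.36 + 400 × 0.252 = 244.8, stated as 245 children with an episode, and exact two-sided Fisher power of 90.2% against the stated 90%. This checks the group size used below but does not bear on SAEs.

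**Inputs from the protocol.**

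- 445 enrolled per arm (Synopsis, Appendix G).
- Control SAE proportion 28.6% over Months 0 to 21 in the earlier trial (Section 1.4).
- Efficacy against severe malaria 57.7% over six months post Dose 3 and 48.6% over the whole study (Section 1.4).
- Efficacy of 30% against clinical malaria assumed for this trial (Section 10.6.1).

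**Assumptions.** Control SAE risk S in this trial: 10% to 28.6%. Malaria share s of control SAEs: 30% to 60%. The protocol gives neither. Efficacy E against malaria is applied to malaria SAEs.

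**Step 1: how large an excess leaves the totals equal?** Take no overlap between causes. The control non-malaria risk is S(1 − s). Malaria risk in vaccinees is sS(1 − E). Equal totals require a vaccinee non-malaria risk of S − sS(1 − E). The offset risk ratio is

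RR = [1 − s(1 − E)] / (1 − s), which does not depend on S.

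- s = 0.3, E = 0.30: (1 − 0.21)/0.70 = 1.13
- s = 0.5, E = 0.577: (1 − 0.2115)/0.50 = 1.58
- s = 0.6, E = 0.577: (1 − 0.2538)/0.40 = 1.87

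With S = 28.6% and s = 50%, malaria SAEs fall from 14.3% to 6.0% at 57.7% efficacy, and non-malaria SAEs can rise from 14.3% to 22.6% with both totals at 28.6%.

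**Step 2: would a direct non-malaria row show it?** Normal approximation, two-sided 5%, n = 445 per arm: power = Φ(d/SE − 1.96), with SE = √{[p₀(1 − p₀) + p₁(1 − p₁)]/445}.

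For 14.3% against 22.6%: d = 0.0825, SE = 0.0258, power = Φ(1.23) = 89%. For S = 10%, s = 30%, E = 30% (7.0% against 7.9%): d = 0.009, SE = 0.0176, power = Φ(−1.45) = 7%.

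| Control SAE risk | Efficacy | Power, share 30% | Power, share 50% | Power, share 60% |
|---|---|---|---|---|
| 28.6% | 57.7% | 43% | 89% | 98% |
| 28.6% | 48.6% | 32% | 78% | 93% |
| 28.6% | 30% | 15% | 41% | 60% |
| 10% | 57.7% | 16% | 42% | 61% |
| 10% | 30% | 7% | 16% | 24% |

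Power is only a yardstick here, since no SAE test is planned.

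**Step 3: check with overlap allowed.** Suppose malaria and non-malaria SAEs occur independently, with a control total of 20%, half of it malaria, and 58% efficacy. Malaria SAEs go from 10.0% to 4.2%, and non-malaria SAEs can rise from 11.1% to 16.5% (RR 1.48) with the total at 20% in both arms. Fisher power at 445 per arm is about 61% for one aggregate non-malaria row. It is about 6% for any one of ten equal preferred terms. The all-cause comparison rejects about 4% of the time, which is type I error only.

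**Step 4: how good is subtraction?** Total minus malaria counts children whose SAEs were all non-malaria and misses those with both kinds. In the Step 3 model with no true excess (non-malaria 11.1% in both arms), subtraction gives 11.1% × 0.900 = 10.0% in controls and 11.1% × 0.958 = 10.6% in vaccinees. It understates both arms and shows a small difference that is not real, because the overlap shrinks when malaria falls.

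**The case against.** Four points weigh on the other side.

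**It may be left to the analysis plan.** Section 6.5 promises a reporting and analysis plan, and Section 5.1.4.1 has the DSMB review it. An extra row and a term list are ordinary content for that plan, and nothing in Sections 10.10.4.1 or 10.11.2 forbids them. That is fair, and the text is not in error. Still, the protocol does fix the SAE display, for three cut-offs, in a form that suits this trial poorly.

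**Nothing is formally compared.** A reader might infer that the plan tests all-cause SAEs between groups, or would declare safety on the total. The documents do not support that: the outputs are descriptive proportions with confidence intervals. Even the all-cause row is implied rather than spelled out. What stands is that readers will set those proportions side by side.

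**The excess is not invisible.** With malaria coded to one term, the total minus the malaria row gives exactly the children with only non-malaria SAEs. In the 28.6% example at a 50% share, the remainder of 14.3% against 22.6% could be read off if nobody had both kinds. Section 8.4 also asks for the diagnosis, not individual symptoms, as the SAE. This largely stands: the gap is an approximate reading where an exact one is available.

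**The large power figures pair mismatched inputs.** The 28.6% covers 21 months in children aged 1 to 4 years, whereas Section 10.10.4.1 stops at about Month 6½. The 57.7% is a six-month estimate for severe malaria, which is not the same as any malaria admission. SAE counting also starts at Dose 1, before the three-dose course is complete. This stands, and it is why the full range is shown.

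The DSMB is informed of all SAEs and causality is assessed for each one. These safeguards work case by case and do not supply the missing summary.

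**Conclusion.** The point holds as a gap in presentation. As specified, the SAE tables do not separate serious events the vaccine is meant to prevent from those it might cause, so an equal or lower total does not exclude an excess spread over several non-malaria terms. The direction follows from the protocol's own definitions. The size does not: the offset risk ratio of about 1.13 to 1.87 and the power of about 7% to 98% rest on an assumed control SAE risk and malaria share, on efficacy figures borrowed from other endpoints and periods, and on no overlap between causes.

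Two further inferences should be resisted. The commonest-cause statement applies to Kilifi children under 18 months and should not be extended to Korogwe. A non-malaria row would also not reliably detect an excess: toward the lower end of the range it would usually miss one. Nothing in the protocol indicates that such an excess exists.

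**What to change.** In Sections 10.10.4.1 and 10.11.2, add the proportion of children with at least one SAE excluding P. falciparum malaria, by group with exact 95% CI. Place it beside an explicit all-cause proportion, to Clinic Visits 6, 7 and 9. Before unblinding for the Visit 6 analysis, list the preferred terms that count as malaria and set a rule for mixed admissions, such as malaria with pneumonia. Use the same list and rule unchanged in the annex analyses, since follow-up after that point is single-blind.

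The cost is one row per SAE table, a short term list and a counting rule applied blind. No new data are needed, and sample size and clinical management do not change.

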**Number of subjects**

890 subjects to be enrolled. It is expected that approximately 800 subjects will be evaluable at study end.

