## 2. OBJECTIVES

### 2.1. Primary objective

**NOTE:** *In the event that malaria rates are lower in the year of the study the cross sectional survey, unblinding and analysis scheduled at 4½ months post Dose 3 will be delayed until approximately 245 children have experienced an episode.*

- For RTS,S/AS01E when administered as 3 doses intramuscularly on a 0, 1, 2-month schedule to children aged 5 to 17 months living in malaria-endemic areas:
  - to assess efficacy against clinical malaria disease meeting the primary case definition (detected on active and passive case detection) with *P. falciparum* over a period of 4½ months (starting two weeks post Dose 3).

Refer to Section 10.1 for definition of the primary endpoint.

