**Appendix G Vaccine supplies, packaging and accountability****1. Vaccine and/or other supplies**

GSK Biologicals will supply the following study vaccines, sufficient number of doses to administer to all subjects as described in the present protocol.

- Sufficient doses for 445 recipients of the candidate vaccine RTS,S/AS01E (doses of RTS,S vaccine in monodose vials and doses of AS01E adjuvant in vials).
- Sufficient doses for 445 recipients of Sanofi-Pasteur's Human Diploid Cell Rabies Vaccine

Amended 20 December 2006

At least an additional 3% of their respective amounts of RTS,S/AS01E and Sanofi-Pasteur's Human Diploid Cell Rabies Vaccine will be supplied for replacement in case of breakage, bad storage conditions or any other reason that would make the vaccine unusable (i.e. given by mistake to another subject).

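### The exact 95% CIs on per-dose reactogenicity percentages ignore that one child contributes up to three doses; with positive within-child correlation they are slightly too narrow (minor).

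*Protocol*

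**What the plan says.** Section 10.10.4.1 of the Protocol plans two families of reactogenicity table, both on the same cohort: "Safety will be analyzed on the Total Vaccinated Cohort".

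The first family counts children. For any local, any general and any adverse event, the percentage of subjects "will be tabulated with exact 95% CI after each vaccine dose and overall". For single symptoms: "The percentage of subjects reporting each individual solicited local and general adverse event during the solicited follow-up period will be tabulated with exact 95% CI".

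In the second family the unit is the dose. For single symptoms: "The percentage of doses followed by each individual solicited local and general adverse event will be tabulated, overall vaccination course, with exact 95% CI". The percentage of doses followed by at least one local event, at least one general event or "by any adverse event will be tabulated, overall vaccination course, with exact 95% CI". Similar tables are announced for Grade 3 events and for relationship to vaccination and, with the single-symptom tables, for fever in half-degree steps.

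Section 2.1 describes the vaccine "when administered as 3 doses intramuscularly on a 0, 1, 2-month schedule". The section names no adjustment for several doses coming from one child.

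**The concern.** The unit in the second family is the dose, pooled over the whole course, but doses are not sampled independently: they come in sets of up to three from one child, given the same product. A child who reacts to one dose may well be more likely to react to another. If so, 1,335 doses carry less information than 1,335 independent observations, and an interval that counts them as independent is too short.

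The Protocol recognises the same structure elsewhere. Section 10.9.2 analyses repeated malaria episodes by Poisson regression with random effects, so within-child dependence is allowed for in efficacy but not in per-dose reactogenicity.

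What is at stake is the stated precision of descriptive tables for a secondary safety endpoint. Per-dose percentages do get read side by side in this programme: section 1.5 sets Grade 3 events after 17.6% of doses with one formulation against 28.4% with another. It is therefore worth having error bars that mean what they say.

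**Working it through.** The Protocol gives no width or coverage for these intervals, so there is no figure of its own to reproduce. Its 90% power statement (section 10.6.1) concerns the primary efficacy comparison and is not touched.

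**Inputs from the Protocol**
- Children per group: 445 (Appendix G: "Sufficient doses for 445 recipients of the candidate vaccine RTS,S/AS01E"). The Synopsis agrees: "890 subjects to be enrolled. It is expected that approximately 800 subjects will be evaluable at study end"; 890 / 2 = 445.
- Doses per child: m = 3 (section 2.1).
- Doses per group: 445 x 3 = 1,335 at most, since the Total Vaccinated Cohort also includes children who did not complete the course.

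**Assumptions, because the Protocol gives no figure**
- Within-child correlation of a reaction across doses, ICC: 0.1, 0.3 and 0.5, with 0 as the reference.
- Percentage of doses followed by an event: 5%, 20%, 50% and 80%.
- "Exact" means Clopper-Pearson, its usual meaning; the Protocol does not use the word binomial.

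**Step 1, design effect.** DE = 1 + (m - 1) x ICC = 1 + 2 x ICC, which gives 1.2, 1.6 and 2.0. The effective number of doses is 1,335 / DE: about 1,112, 834 and 668.

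**Step 2, width.** The interval should widen by about the square root of DE: 1.095, 1.265 and 1.414. Clopper-Pearson limits computed on the effective number of doses, at 20% of doses (267 of 1,335), are:

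| ICC | DE | 95% interval | Width (points) | Ratio to planned |
|---|---|---|---|---|
| 0 (as planned) | 1.0 | 17.9-22.2% | 4.36 | 1.00 |
| 0.1 | 1.2 | 17.7-22.5% | 4.79 | 1.10 |
| 0.3 | 1.6 | 17.3-22.9% | 5.54 | 1.27 |
| 0.5 | 2.0 | 17.0-23.2% | 6.21 | 1.42 |

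The lower limit moves by 0.2 to 0.9 points (17.9 to 17.7, or to 17.0). The upper limit moves by 0.3 to 1.0 points (22.2 to 22.5, or to 23.2). At 50% of doses the planned width of 5.43 points becomes 5.96, 6.89 and 7.72.

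**Step 3, coverage of the planned interval.** A normal approximation gives coverage = 2 x Phi(1.96 / sqrt(DE)) - 1:
- ICC 0.1: 1.96 / 1.095 = 1.79, coverage about 92.6%
- ICC 0.3: 1.96 / 1.265 = 1.55, coverage about 87.9%
- ICC 0.5: 1.96 / 1.414 = 1.39, coverage about 83.4%

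A beta-binomial simulation (each child draws a personal reaction probability, then three doses; 40,000 trials per setting; Clopper-Pearson on all doses) agrees. Ranges are over the four event rates:
- ICC 0: 95.2-95.6%
- ICC 0.1: 92.8-93.4%
- ICC 0.3: 88.0-88.8%
- ICC 0.5: 83.5-84.4%

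With 400 children per group the results are nearly the same.

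**Step 4, would two groups look different by mistake?** Two identical groups of 445 children were simulated (20,000 runs; 5%, 20% and 50% of doses) and the share of runs with non-overlapping intervals was counted: 0.4-0.5% at ICC 0, 0.8-1.1% at 0.1, 2.4-2.7% at 0.3 and 4.3-5.0% at 0.5.

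**The case against.** The strongest reply is that nothing rests on these intervals. They are descriptive; no hypothesis, sample size, stopping rule or decision uses a per-dose interval, and the point estimates do not change. That stands, and it is the main reason the point is minor.

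Second, valid intervals stand in the same section. The subject-level tables have one observation per child and are sound, including those after each dose. This also stands, with one limit: the by-dose breakdown is written out for any local, any general and any adverse event, but not expressly for each single symptom.

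Third, the size is assumed. The Protocol has no data on how strongly reactions repeat within a child. At zero correlation the planned interval is correct, and at 0.1 coverage is still about 93%. This stands too: the mismatch between method and unit is certain, but the amount is not.

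Fourth, section 6.5 foresees a reporting and analysis plan that could refine the method. This carries less weight, because the Protocol itself already fixes the unit, the pooling and the exact interval.

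A reader might go further and infer that the tables will often show false differences between vaccine groups. The documents do not support that. Section 10.10.4.1 plans no between-group comparison of these intervals. Even if a reader made one, non-overlap of two 95% intervals is a conservative criterion: the false rate does rise from about 0.5%, but it stays at or below about 5% over the whole assumed range.

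**Conclusion.** The point holds as a minor one. An interval that assumes independent doses is specified for data with up to three doses per child, and under any positive within-child correlation it understates the uncertainty. Over an assumed correlation of 0.1 to 0.5, true coverage is about 93% down to 84%, and a correct interval is about 10% to 42% wider. In percentage points this is small: at 20% of doses, a fraction of a point to about one point at each limit, which is unlikely to change how the safety profile is read.

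The conclusion rests on reading "exact" as Clopper-Pearson, on close to three doses per child, and on positive correlation. It does not extend to the point estimates, the subject-level intervals, the efficacy analyses or the power statement.

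**What to change.** In section 10.10.4.1, for percentages of doses only, replace the exact interval with one that treats the child as the cluster. Three options would do: a robust-variance (GEE) interval with child as cluster, a bootstrap that resamples children, or a Clopper-Pearson interval computed on the number of doses divided by an estimated design effect. The last stays closest to the present wording and suits rare events such as Grade 3 symptoms.

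Alternatively, show per-dose percentages without an interval and let the subject-level exact intervals carry the statement of precision. In that case, say expressly that single solicited symptoms are also tabulated by subject after each dose.

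The cost is a small change in the table programs and slightly wider intervals. No new data, visits or subjects are needed.
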